## Abstract

**Introduction:**

Multiple Sclerosis (MS) is the most common neuroimmunological disease in women of childbearing age. Current MS therapy consists of immunomodulatory relapse prevention with disease-modifying therapies (DMTs) and acute relapse therapy with the synthetic glucocorticoid (GC) methylprednisolone (MP). As most DMTs are not approved for use during pregnancy, treatment is usually discontinued, increasing the risk for relapses. While MP therapy during pregnancy is considered relatively save for the fetus, it may be detrimental for later cognitive and neuropsychiatric function. The underlying mechanism is thought to be an epigenetically mediated desensitization of GC receptors, the subsequent increase in stress sensitivity, and a GC-mediated impairment of brain development. The aim of this study is to investigate the associations of fetal MP exposure in the context of MS relapse therapy with later cognitive function, brain development, stress sensitivity, and behavior.

**Methods and Analysis:**

Eighty children aged 8–18 years of mothers with MS will be recruited. Forty children, exposed to GC in *utero* will be compared to 40 children without fetal GC exposure. The intelligence quotient will serve as primary outcome. Secondary outcomes will include attention, motor development, emotional excitability, Attention-Deficit Hyperactivity Disorder-related symptoms, and behavioral difficulties. The Trier Social Stress Test will test stress sensitivity, EEG and MRI will assess functional and structural brain development. To determine underlying mechanisms, DNA methylation of the GC receptor gene and the H19/IGF2 locus and changes in the microbiome and the metabolome will be investigated. Primary and secondary outcomes will be analyzed using linear regression models. Time-variant outcomes of the stress test will be analyzed in two mixed linear models exploring overall activity and change from baseline.

**Ethics and Dissemination:**

This study was approved by the participating institutions' ethics committees and results will be presented in accordance with the STROBE 2007 Statement.

**Trial Registration:**

https://clinicaltrials.gov/ct2/show/NCT04832269?id=ZKSJ0130

## Introduction

### Background

Multiple sclerosis (MS) is one of the most common neurological diseases in young adults, usually occurring between the ages of 20 and 40 years, affecting an estimated 2.8 million patients worldwide (1). Approximately two thirds of these patients are women, mainly of childbearing age (2). Therapy for MS consists of disease-modifying therapy (DMT) for relapse prophylaxis with immunomodulatory substances and relapse therapy with methylprednisolone (MP). As most immunomodulators are not approved for use during pregnancy, treatment is usually discontinued with a subsequent risk increase for relapses (3). While the risk for relapses especially during the first and second trimester is comparable to the prepartum period and thus not an uncommon event, the risk decreases by ~70% during the third trimester (4). Based on these data and the prevalence rate for MS in women of childbearing age (1), we estimate that in Germany ~5,500 MS-relapses occur annually during a pregnancy.

European and US guidelines recommend the use of high-dose MP to treat severe, disabling relapses anytime during pregnancy with a risk-benefit-evaluation between gestational weeks 8 and 11 (5). This treatment is considered relatively harmless for the fetus since no severe physical development disorders have been found at birth (3, 6). However, studies with offspring antenatally exposed to the synthetic GC betamethasone (BM) to enhance fetal lung maturation due to a threat of premature labor suggest a risk for increased stress sensitivity and neuropsychiatric disorders in later life (7, 8). These effects of antenatal GC-exposure on offspring outcomes have been found at all periods of pregnancy (9). Remarkably, the treatment regime used in obstetric indications consists of only 2 × 8–12 mg BM 24 h apart as compared to the 500–1,000 mg MP over 3 – 5 days used to treat an MS relapse. Considering the ~six-fold higher biological activity of BM compared with MP (10), the total dose of GC in the treatment of MS relapses is up to 50-fold higher than for obstetric indications. In a previous study from our workgroup, which is the basis for the present study, we could show that antenatal exposure to 2 × 8 mg BM to enhance fetal lung maturation resulted in multidimensional changes in neurodevelopment and stress-sensitivity in full-term offspring at 8–9 years of age compared to children not exposed to BM (11, 12). This included an intelligence quotient (IQ), which was on average 10 points lower in the exposed group than in the non-exposed group, changes in autonomic activity, attention-deficit hyperactivity disorder (ADHD)-like symptoms and changes in electrocortical activation during a cognitive task. In a follow-up study with 16-year-olds antenatally exposed to BM, we found changes in measures of structural brain development, specifically alterations in gyrification and a reduced cortical thickness in MRI scans (publication in preparation). Combined, these findings have led to a change in German obstetric guidelines already, which now call for a more critical indication for the induction of lung maturation (13, 14).

The adverse long-term effects of antenatal GC exposure may be the result of both a programming of the function of the hypothalamic-pituitary-adrenal axis (HPAA) and maturational effects of GCs on functional and structural brain development. The relationship between adverse environmental influences such as an intrauterine exposure to supraphysiological levels of GCs during critical periods of development and the health of the offspring in later life is the basis of the “Fetal Programming” or “Developmental Origins of Health and Disease (DOHaD)” hypothesis (15, 16). Until the 3^rd^ trimester, the fetus is incapable of synthesizing cortisol and relatively protected from maternal cortisol because the placental enzyme 11ß-HSD 2 inactivates 80–90 % of maternal cortisol to cortisone (17). In contrast to cortisol, most synthetic GCs with the exception of MP are no substrates for 11ß-HSD2 and cross the placenta without inactivation (18). However, even though MP is a substrate for 11ß-HSD 2, high bolus doses of MP as used in MS-relapse therapy rapidly saturate this enzyme and reach the fetus in pharmacological concentrations (6, 19). Once in the fetal circulation, even short-term elevated levels of GCs can permanently change patterns of gene expression and cellular function via epigenetic mechanisms (20). Permanent desensitization of GC receptors involved in negative feedback regulation of the HPAA via DNA methylation of the promoter region of the GC receptor gene *NR3C1* may lead to a life-long hyperactivity of the HPAA and, thus, to increased stress sensitivity in later life (21, 22). Hyperactivity of the HPAA is associated with stress-related neuropsychiatric disorders, including anxiety, depression, and ADHD (21, 22).

Increased levels of GCs induce accelerated tissue differentiation and maturation at the expense of tissue growth (23). While this effect is utilized to induce lung maturation in fetuses at risk of premature birth (24), it occurs in all organ systems and is reflected in a reduced birth weight following antenatal GC treatment (25). Out of all organ systems, the developing brain is particularly vulnerable to elevated GC concentrations due to its complex sequence of precisely coordinated steps of maturation and its intrinsic plasticity (26), a basic property of the brain enabling learning and adaptation. Supraphysiological concentrations of GCs change fetal brain development via antiproliferative effects on neural stem and progenitor cells (27). The subsequent changes in neuronal connections and myelination (28, 29) may contribute to the sustained changes in cognitive and cerebral functioning. Increased concentrations of GCs may also affect fetal brain development indirectly via changes in the composition of the maternal gut microbiota (30, 31), which in turn modulates the fetal gut microbiota (32, 33). The gut microbiome communicates with the central nervous system via an integrated, bidirectional communication pathway which i.a., involves inflammatory cytokines, neuromodulators and neurotransmitters (17, 34, 35). Consequently, disturbances in this communication system, the so-called “gut-brain” axis, have been associated with a number of neurological and psychiatric diseases, such as depression, anxiety disorders, and attention deficit hyperactivity disorder (17, 32, 36, 37).

While no studies examining the long-term effects on the offspring exist, current MS guidelines consider relapse therapy using MP during pregnancy safe for the fetus. Based on findings regarding long-term consequences of antenatal BM exposure, we hypothesize however, that this may not be the case. Based on the up to 50-fold cumulative dose of GCs in MS relapse treatment and its more prolonged administration compared to obstetric indications, we aim to investigate whether relapse treatment with MP in MS patients during pregnancy affects structural and functional brain development, cognition and behavior as well as stress sensitivity in the antenatally exposed offspring.

### Research Aims and Hypotheses

This study is based on two hypotheses: Fetal exposure to MP during MS relapse therapy leads to epigenetically mediated

a. disturbances in functional and structural brain development andb. a long-term change in stress sensitivity of the offspring.

The resulting changes in brain function are associated with neuropsychiatric abnormalities as well as cognitive and behavioral changes in later life.

The primary objective of this cross-sectional study is to elucidate associations of antenatal MP exposure with cognitive performance in children aged 8–18 years compared to non-exposed children of mothers with MS. As secondary objectives, this study will investigate the association of cognitive development and behavioral problems with underlying changes in stress sensitivity and functional and structural brain development. To clarify potential epigenetic mechanisms underpinning these changes in stress sensitivity and functional and structural brain development, DNA methylation at the promotor region of the GC receptor gene *NR3C1* and at the H19/IGF2 locus, which controls expression of the insulin-like growth factor 2 (IGF2), the major growth hormone during development (38), will be investigated. To elucidate further potential mechanisms, changes in the composition of the microbiome will be examined.

This study is expected to advance the understanding of developmental programming effects of antenatal high-dosage GC exposure. Another major aim of this study is to add data to the debate around evidence-based decision-making regarding (1) the continuation of a DMT during pregnancy *vs*. the potential long-term risks of relapse therapy with MP for the child's cognitive and neuropsychiatric health in later life, and (2) the risks of relapse treatment with MP for the child *vs*. the risks of an untreated relapse for the mother. There is an accumulating amount of *real world* data on the safety of continuing a DMT during pregnancy primarily with interferons or glatiramer acetate, which may be safer for mother and child than a potentially necessary relapse treatment with MP.

## Methods and Analysis

### Study Design

This two-center, observational, cross-sectional study aims to recruit *N* = 80 children of mothers with MS. The exposed group (*n* = 40) will consist of children who were antenatally exposed to MP as part of maternal MS relapse therapy, while the control group (*n* = 40), will consist of children of mothers with MS, who were not exposed to MP. Assessment will take place at the University Hospital in Jena (UKJ) and the Ruhr University Bochum (RUB). The first participant was included on 19/10/2020 and the study is anticipated to continue until the end of 2024.

### Sample Size

The aforementioned study by some of the authors (11) investigated cognitive performance, as measured by an IQ test, in two groups of 39 healthy children at the age of 8 years. Considering the lower biological activity of MP compared to BM, the cohort in the present study was exposed to a GC-dose up to 50-fold higher than in the study on the effects of BM. The higher dosage of MP will most likely expose a significant effect in two groups of the same size as the previous study.

As the present study uses a different IQ test, the planned sample size is further based on the standardized effect size Cohen's *d*, as a multiple of the standard deviation. The previous study found a mean difference in IQ score of 10.5 points (SD = 14.0). A two-sample *t*-test (α = 0.05) would have sufficient power of 82% (*d* = 0.71) to 87% (*d* = 0.75) with two groups of 35 children. This takes into account potential non-evaluability of five participants per group, e.g., in the case of artifacts or attrition. The planned regression models include seven variables, which, based on the *rule of ten* leads to a sufficient number of cases to produce robust results (39).

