### Data Analysis Plan

For the analysis of the primary outcome, exposed and non-exposed groups will be compared in terms of their performance on the IQ test using a linear regression model taking into account potential confounders, including antenatal exposure to MP, point in time of exposure, maternal age at birth, birth weight, and socioeconomic background. Exploratory analysis of secondary outcomes will be performed with a linear regression model. Those outcomes measured repeatedly throughout the course of the TSST-C will be evaluated as time series data with a linear mixed model, with time as a further independent factor. For this analysis, two models will be fitted to explore (1) overall mean activity throughout the TSST-C, as well as (2) the change from baseline, in which the stress response will be adjusted to the baseline value.

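### The stated 82–87% power belongs to an unadjusted t-test; power for the exposure coefficient of the primary regression is not established, and the point-in-time term is the main threat to it

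*Protocol article*

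**What the plan says.** All places are in the Protocol article.

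- **Sample Size, effect.** "The previous study found a mean difference in IQ score of 10.5 points (SD = 14.0"), which gives d = 10.5/14.0 = 0.75. The origin of the second value, 0.71, is not given.
- **Sample Size, power.** A two-sample t-test at α = 0.05 "would have sufficient power of 82" per cent at d = 0.71 and 87% at d = 0.75, with 35 children in each group. The recruitment target of 40 per group allows for losses: "This takes into account potential non-evaluability of five participants per group".
- **Sample Size, regression.** "The planned regression models include seven variables", and a rule of ten cases per variable is cited for the robustness of the results.
- **Data Analysis Plan.** For the primary outcome the groups will be "compared in terms of their performance on the IQ test using a linear regression model". The model terms named are MP exposure, point in time of exposure, maternal age at birth, birth weight and socioeconomic background. The list is introduced as an inclusive one.
- **Table 1, basic pregnancy and birth data.** The pregnancy week of relapse and treatment is recorded for exposed children.
- **Background.** Antenatal glucocorticoid treatment is described as being reflected in lower birth weight.

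**The concern.** The power statement and the primary analysis concern different quantities. The t-test compares two raw means. The regression tests the exposure coefficient given the other terms, and its precision depends on two things that a t-test calculation leaves out: how far the other terms predict exposure, which costs power, and how far they predict IQ, which gains it.

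This is an observational comparison, matched only on age and sex, so some relation between covariates and exposure is to be expected. Two named terms are tied to exposure by the article's own account. Timing has a value only in exposed children, and birth weight is described as lowered by glucocorticoids. The section mentions the regression but links it to the sample size only through the rule of ten, which contains no effect size, α or variance and so cannot carry the power figure across.

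At stake is how the adjusted result is read. A confidence interval that includes zero would be set against a stated power of 82–87% that nobody has derived for that coefficient.

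**Working it through.** **Inputs from the article.** α = 0.05 (sidedness not stated); d = 0.71 and 0.75; 35 evaluable per group, 70 in all; seven model terms.

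**Inputs not in the article, therefore assumed.** R2x, the share of variance in exposure explained by the other terms; R2y, the share of within-group IQ variance they explain; the distribution and coding of timing.

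**Step 1. Reproduce the stated figure.** Two-sided t-test, df = 68, non-centrality = d × √(35/2) = d × 4.183.

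- d = 0.71: non-centrality 2.970, power 83.3%.
- d = 0.75: non-centrality 3.137, power 87.1%.

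Both are within 2 points of the stated 82% and 87%. A one-sided test would give 90.2% and 92.8%, so the plan's figures are two-sided.

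**Step 2. Exposure coefficient in a seven-term regression.** df = 70 − 7 − 1 = 62, and

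non-centrality = d × 4.183 × √[(1 − R2x)/(1 − R2y)].

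| R2x | R2y | Power, d = 0.71 | Power, d = 0.75 |
|---|---|---|---|
| 0 | 0 | 83.2% | 87.0% |
| 0.1 | 0 | 79.2% | 83.4% |
| 0.2 | 0 | 74.4% | 78.9% |
| 0.3 | 0 | 68.7% | 73.4% |
| 0.3 | 0.2 | 78.1% | 82.4% |
| 0.3 | 0.3 | 83.2% | 87.0% |
| 0.1 | 0.2 | 87.3% | 90.6% |
| 0.1 | 0.3 | 91.2% | 93.8% |

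The lost degrees of freedom alone cost about 0.1 point. Power equals the t-test figure when R2x and R2y are about equal, falls below it when R2x is larger and rises above it when R2y is larger.

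**Step 3. The timing term, coded as week in the exposed and 0 in controls.** With equal groups, and timing with mean m and variance v among the exposed, the squared correlation of timing with the exposure indicator is

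R2x = m² / (m² + 2v).

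This counts timing alone; other covariates can only add to it. For weeks spread evenly over whole weeks (assumed), df = 62:

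| Weeks | m | v | R2x | Power at R2y = 0 (d = 0.71 / 0.75) | Power at R2y = 0.3 |
|---|---|---|---|---|---|
| 1–40 | 20.5 | 133.25 | 0.61 | 44.5% / 48.6% | 58.6% / 63.3% |
| 4–36 | 20 | 90.67 | 0.69 | 37.2% / 40.7% | 49.7% / 54.1% |
| 4–26 | 15 | 44 | 0.72 | 34.1% / 37.4% | 45.8% / 49.9% |

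First row worked: 20.5² = 420.25; 420.25/(420.25 + 266.5) = 0.61.

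Under this coding the exposure coefficient is the difference extrapolated to week 0. The table supposes that this difference has the same d, which nothing in the article supports.

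Trimester indicators with a first-trimester reference (assumed split 14/14/7) inflate the variance by (1/14 + 1/35)/(2/35) = 1.75. Power is then 60/65% at R2y = 0 and 75/80% at R2y = 0.3.

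**Step 4. Timing centred among the exposed, 0 in controls.** The centred term averages zero in both groups, so it is uncorrelated with exposure and adds almost no inflation. The coefficient is again the average group difference. The article does not say that timing will be centred.

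**The case against.** The other side has a good deal right.

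- **The figure is labelled honestly.** The article names the t-test, and the arithmetic is correct. Planning on a t-test and analysing with an adjusted model is common. This stands: there is no arithmetic error.
- **A reader might infer that the regression lacks the stated power.** The documents do not support that. Neither R2 is given, and setting R2y = 0 is pessimistic for variables the plan itself treats as potential confounders. Modest adjustment could well raise power.
- **A reader might infer that seven terms contradict the five named.** The list of five is expressly open, so this is not a contradiction.
- **A reader might infer that the rule of ten fails by its own standard.** 70/7 = 10 meets it exactly. It would fail only if multi-category terms had been counted as one each, and nothing shows that. The rule is also offered for robustness, not for power.
- **A reader might infer that a null result is bound to be taken as proof of safety.** The stated aims are to study associations and to add data to a debate, so this is a risk of reading and not something the article claims.
- **The low figures under zero coding are not the power of the powered contrast.** That is true, because the coefficient has changed meaning. It also shows why the t-test figure does not carry over to the model as listed. A coding choice could be left to an analysis plan, but the article does name timing as a term of the primary model beside exposure.

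**Conclusion.** The 82–87% is correct for an unadjusted two-sided t-test and is not established for the primary regression's exposure coefficient. For ordinary covariates the direction is open: over the assumed values shown, power runs from 69/73% to 91/94%.

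The document-based threat is the timing term. If it enters as week with 0 for controls, power is about 34–49% at R2y = 0 and about 46–63% at R2y = 0.3, and the coefficient is no longer the average difference behind d. These figures depend on the assumed week ranges and on that coding; centring removes the problem. Birth weight is a lesser concern of the same kind. If glucocorticoids lower it, it is related to exposure, and adjusting for it may also take out part of the effect under study.

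This should be corrected, but it does not call the sample size into question.

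**What to change.** 1. Take point in time of exposure out of the primary model and analyse it within the exposed group. Alternatively keep it, centred among the exposed and 0 for controls, and say so.
2. Leave birth weight out of the primary model, or keep it for a sensitivity analysis.
3. Restate power for the adjusted exposure coefficient over a stated range of R2x and R2y, with df matching the terms kept. If two of the seven go, df = 70 − 5 − 1 = 64. If timing is kept centred and only birth weight goes, df = 63. The t-test figure can stay beside it, labelled as unadjusted.
4. Present the rule of ten only as a check on model stability.

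The cost is one rewritten paragraph on sample size and one sentence in the analysis plan. The stated power becomes a range whose lower end may be less favourable than 82%. No change in the number of children is needed.

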### Sample Characteristics and Recruitment

Children aged 8–18 years, of any sex and ethnicity are eligible to participate. Based on the children we identified for the group exposed to GC, control children are matched 1:1 by age and sex. A physician presents verbal and written information about the study, its aims, the procedure, and data management to the participants and their guardian(s) and answers any remaining questions. Children are included if they speak German and they and their guardian(s) are willing and able to consent to their participation.

Exclusion criteria for both groups comprise preterm birth (before 34^th^ week of gestation), a birth weight below the 5^th^ percentile, and perinatal complications, such as cerebral hemorrhage, neonatal intensive care requiring ventilation, or any further antenatal therapy with GCs beyond MS relapse therapy. Participants are further excluded from the study in case of maternal substance abuse during pregnancy or serious illness in the child which makes assessment impossible, such as an intellectual disability, or long-term medication with GCs, e.g., in asthma.

Recruitment takes place in the UKJ's close cooperation with the RUB, the host of the *German MS and Pregnancy Registry*, and several other MS centers across Germany. A search algorithm was developed to identify eligible participants for the MP-exposed and the control group within the respective hospital-specific data management systems. Further recruitment efforts are directed toward online advertisements on MS-specific websites and UKJ's public outreach channels.

